## Methods/design

### Objectives and design

This parallel, two-arm, single-center, prospective, single blind (investigator-initiated, assessor-blinded), randomized, controlled trial tests the hypothesis that applying sufficient PEEP without RM right after patients are turned into lateral decubitus position is an effective strategy for patients receiving one lung ventilation. 84 patients will be randomly divided into one of two different groups (see Consolidated Standards of Reporting Trials [CONSORT] diagram, Fig. 1). The SPIRIT 2013 Checklist is given in Additional file 1.

**Fig. 1 Fig1:**
[figure not shown]
Consolidated standards of reporting trials (CONSORT) diagram of this trial. *DLT* double lumen tube, *COPD* chronic obstructive pulmonary disease, *ASA* American society of anesthesiologists, *OLV* one lung ventilation, *ARDS* acute respiratory distress syndrome, *Qs/Qt* fraction of intrapulmonary shunt

This trial will be conducted at Peking University Third Hospital, Beijing, China. The study complies with the CIOMS Principles of the International Guidelines for Biomedical Research Involving Human Subjects and the WMA of the Declaration of Helsinki. The study has obtained ethics approval from the Ethics Committee of Peking University Third Hospital (The approval number is 2023–614-03) and has been registered in the Chinese Clinical Registry (Chictr) (registration number: ChiCTR2400080682).

### Blinding, data collection, randomization and record keeping

This is a single-blind randomized clinical trial. Demographic data, results of laboratory tests, history of previous illnesses, fluid balance, hemodynamic variables, anesthesia-associated variables, respiratory parameters and postoperative clinical status will be collected and recorded onto case report forms (CRF). All patients meeting the inclusion criteria will be randomly allocated to the study group and the control group in a ratio of 1:1. Randomization will be carried out by means of a computer-generated blocked randomization form, with 17 blocks of five patients per block. Allocation will proceed with opaque, sealed and numbered envelopes. Subjects will be recruited and assigned in numeric order. All original records (CRF and associated correspondence) will be archived and safeguarded for 10 years and then destroyed, as required by hospital standards.

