### Sample size calculations

The primary endpoint of this study is oxygenation index measured at T4. According to literature [16], oxygenation index for patients inhaling pure oxygen and under well oxygenated conditions during TLV usually ranges between 350-400 mmHg and drops to 150-200 mmHg after patients are switched to OLV. Therefore, during OLV, changes in oxygenation index within the limit of 50 mmHg would be clinically insignificant. Thus, the cut-off value for inferiority is set to 50 mmHg. In other words, in our study, if oxygenation index measured at T4 of the study group is below that of the control group, but the difference between that of the two groups is within 50, then the ventilation strategy of the study group is not inferior to that of the control group in terms of improving intraoperative oxygenation. We set probability of type 1 error at α = 0.025, probability of type 2 error at β = 0.20, and power value at 0.80; a sample size of 38 is calculated for each group by using PASS 11.0 software. Considering a 10% removal and dropout rate, a final sample size of 42 is required for each group.

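### Blocks of five cannot be split equally between two arms, so the stated list of 17 such blocks (85 places) does not secure the planned 1:1 allocation of 84 patients at 42 per group

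*Protocol article*

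**What the plan says.** Under Objectives and design, the protocol article sets out the layout ("This parallel, two-arm, single-center, prospective, single blind") and the total ("84 patients will be randomly divided into one of two different groups").

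Under Blinding, data collection, randomization and record keeping, patients are to be "randomly allocated to the study group and the control group in a ratio of 1:1". The device is a "computer-generated blocked randomization form, with 17 blocks of five patients per block", delivered by numbered sealed envelopes used in sequence.

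Under Sample size calculations, "a sample size of 38 is calculated for each group by using PASS 11.0 software", and after the allowance for dropout, "a final sample size of 42 is required for each group".

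The article mentions no third arm and no planned unequal ratio. It gives no rule for dividing an odd block and does not account for an 85th place.

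**The concern.** Permuted blocks are used so that the arms are equal at the end of every block and nearly equal in between. With two arms at 1:1, a block can be balanced only if its size is even. The stated size is odd, so no complete block is balanced, and the block count and block size together do not give the stated total.

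This is not detail left to another document. The article states the block size, the number of blocks, the ratio and the per-group size, and these four statements do not fit together.

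Two things are at stake. First, the 42 per group in the sample size section is not a property of the list as described. Second, nobody can rebuild or audit the list from the text: either the block size is misreported, or the list was built with unequal blocks by a rule that is not given.

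**Working it through.** **Inputs, all from the protocol article.** Two arms, ratio 1:1, 17 blocks of 5, total 84, 42 per group, 38 evaluable per group, 10% dropout, α = 0.025, power 0.80.

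**1. The plan's own total.** 38 × 1.1 = 41.8, rounded up to 42; 2 × 42 = 84. The stated 84 is reproduced. (Dividing instead, 38 / 0.9 = 42.2, would round up to 43; that does not affect this point.)

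**2. Places on the list.** 17 × 5 = 85. In the other direction, 84 / 5 = 16.8, so 17 is the smallest number of blocks of five that covers 84 patients. The block count thus agrees with a block size of five. Changing five to four or six alone would not repair the sentence, since 17 × 4 = 68 and 17 × 6 = 102.

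**3. Split within a block.** 5 / 2 = 2.5, so a block is 3:2 or 2:3 at best. Over 17 blocks the total is odd, and the closest possible split of 85 is 43:42.

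**4. Split at patient 84, block direction random.** *Assumption:* each block is 3:2 or 2:3 with probability 1/2, and the last place on the list is unused. After 16 blocks, one arm has 32 + K patients, with K binomial(16, 1/2). The four used places of block 17 add 1, 2 or 3 patients to that arm with probabilities 0.2, 0.6 and 0.2. Combining these exactly:

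| Split at patient 84 | Difference | Probability |
|---|---|---|
| 42:42 | 0 | 0.188 |
| 43:41 | 2 | 0.337 |
| 44:40 | 4 | 0.243 |
| 45:39 | 6 | 0.140 |
| 46:38 | 8 | 0.063 |
| 47:37 or wider | 10 or more | 0.029 |

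Each unequal row covers both directions. The mean absolute difference is 3.30 patients, and a difference of 6 or more has probability 0.232.

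**5. Split at patient 84, block direction alternating.** This is the most favourable simple rule, and the article does not describe it. Sixteen blocks give 8 × 3 + 8 × 2 = 40 in each arm. The last four patients then split 2:2 only if the unused place belongs to the arm with three, which has probability 3/5 = 0.6.

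**6. Effect on power.** The article gives no SD, so I start from its stated 80% power at equal arms. In the normal approximation, the noncentrality there is 1.960 + 0.842 = 2.802. With the same total and the same proportional loss in both arms, a split p : (1 − p) multiplies this by √(4p(1 − p)), whatever the SD.

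- 45:39: 4 × 45 × 39 / 84² = 0.995; root 0.997; noncentrality 2.794; power Φ(2.794 − 1.960) = 79.8%.
- 48:36: 4 × 48 × 36 / 84² = 0.980; root 0.990; noncentrality 2.773; power 79.2%. Under step 4, a split this wide or wider has probability 0.007.

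**The case against.** The strongest reply is that 1:1 describes assignment probability, not the final count. If each odd block leans either way with equal chance, every patient still has probability 1/2 of each arm, just as under simple randomization, which does not secure 42:42 either. The planned t test does not need equal arms, and the likely imbalance is a few patients in 84. One spare numbered envelope does no harm.

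Most of this stands. It is why the point is that the scheme does not secure the balance, and not that the balance can never occur. It is also why the 85-versus-84 gap is only a minor part. What the reply does not remove is the conflict in the text. A blocked list is chosen in order to fix the balance, the article requires 42 in each group, and the random-direction rule that would keep the probability at 1/2 is stated nowhere.

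A reader might also infer something stronger: that one arm takes three places in every block, so that a 3:2 trial (51:34 over 85 places) would be reported as 1:1. The documents do not support this. No such rule appears, and the stated 1:1 ratio contradicts it. Nor do they support a claim of bias or of serious power loss. Even that hypothetical 51:34 split would, by the formula in step 6 (4 × 0.6 × 0.4 = 0.96), leave power at about 78%.

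**Conclusion.** The point holds as an internal inconsistency in the randomization section. Two facts need no assumption: a block of five cannot be 1:1 between two arms, and 17 such blocks make 85 places, which cannot be 1:1 and do not match 84.

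The size of the consequence does rest on assumptions. With random block direction and a stop at patient 84, exact 42:42 occurs in about 19% of lists and the mean difference is about 3.3 patients. With alternating blocks, 42:42 has probability 0.6. The power figures take the article's 80% at equal arms as given and assume equal proportional loss. On that basis the loss is a fraction of a percentage point for the likely splits and under one point at 48:36.

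The matter is therefore one of a correct and auditable description of the allocation. It does not threaten the trial's validity, but it is worth correcting because the correction costs almost nothing.

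**What to change.** Correct the randomization section to say that blocks are of even size, consistent with 1:1 and a total of 84. Randomly varied even sizes would serve. The exact sizes and their order should be kept in a restricted document, because publishing them discloses the structure of the list. For a list issued from the first patient, several constructions give exactly 42:42, for example 21 × 4 = 84 or 14 × 6 = 84.

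What else is needed depends on what was done. By the Trial status section, enrolment was to start on March 1, 2024, before the article appeared on July 22, 2024, so some envelopes may already have been used.

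- **If the actual list used even blocks,** correct the sentence. Nothing else changes.
- **If blocks of five were used,** issue even blocks for the envelopes still unused, leave existing allocations as they are, and report how the odd blocks were split and the ratio actually generated. Even blocks from that point limit further drift. They do not undo an imbalance already present, so exact 42:42 should not be promised.

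The cost is one corrected sentence and, in the second case, a new computer list and envelopes for the remaining patients. The sample size and the planned tests are unaffected.

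### Seventeen blocks of five cannot guarantee the stated 1:1 allocation with 42 patients per arm, and they make 85 slots for 84 patients.

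*Protocol article*

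**What the plan says.** The section on blinding, data collection, randomization and record keeping says that patients are "randomly allocated to the study group and the control group in a ratio of 1:1". Its next sentence describes a computer-generated blocked list "with 17 blocks of five patients per block". Allocation is by opaque, sealed, numbered envelopes used in sequence.

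The totals are given elsewhere. Objectives and design states that "84 patients will be randomly divided into one of two different groups", and the Abstract gives the same total. Sample size calculations starts from 38 per group, allows for 10% loss, and concludes that "a final sample size of 42 is required for each group".

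The article mentions no varying block sizes, no rule for which arm receives the third place in a block, no spare envelope and no truncation of the list at 84.

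**The concern.** Blocking is used so that the arms are equal at the end of every complete block. With two arms at 1:1 this needs an even block size. A block of five leaves every complete block unbalanced by one patient, and the final arm sizes then depend on a rule that the article does not give. The block count and block size also multiply to a total that differs from the planned enrolment.

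What is at stake is mainly whether the allocation can be reproduced and audited. From this description a reader cannot tell how the list was built or what arm sizes to expect. This is not a detail that an article leaves to a fuller document: the block size and count are stated, and they conflict with the ratio and totals stated beside them.

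**Working it through.** **Inputs.** Ratio 1:1 and 17 blocks of five (randomization section); 84 patients (Abstract, Objectives and design); 38 per group before loss, 10% loss, 42 per group after, one-sided alpha 0.025, power 0.80, margin 50 mmHg (Sample size calculations).

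**The plan's own total.** 38 x 1.10 = 41.8, rounded up to 42, and 2 x 42 = 84. This reproduces the stated figure. (Dividing instead, 38/0.90 = 42.2, would round up to 43. That is a separate matter, and 42 is taken as the target here.)

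**The block list.**
- Slots: 17 x 5 = 85, one more than 84.
- Whole blocks: 84/5 = 16.8, so 84 does not fill whole blocks of five.
- Within a block: the closest split is 3:2 or 2:3.
- Over the full list: 85 is odd, so the arms cannot be equal under any rule.

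**Arm sizes under the possible rules (none is stated).**
- *Direction alternates:* 9 x 3 + 8 x 2 = 43 against 9 x 2 + 8 x 3 = 42. With the last slot unused this becomes 42:42 or 43:41, depending on which arm that slot held.
- *Direction random per block (assumption):* the difference in arm sizes is a sum of 17 independent steps of +1 or -1, so its SD is sqrt(17) = 4.1. For a difference of 5 or more, at most 6 of the 17 blocks favour one arm: 2 x (1 + 17 + 136 + 680 + 2380 + 6188 + 12376)/2^17 = 2 x 21778/131072 = 0.33. For 7 or more: 2 x 9402/131072 = 0.14. The difference is 3 or less with probability 0.67. If only the first 84 slots are used, exactly 42:42 has probability 0.188.
- *Same arm always receives three:* 51:34. This contradicts the stated 1:1 and serves only as an outer bound.

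**Effect on power.** The article gives no SD. With n per group = 2(1.96 + 0.84)^2 SD^2 / 50^2 and no true difference, an SD of 76.8 to 77.7 mmHg returns 38; 77.5 is assumed below. Power is Phi(50/SE - 1.96), with SE = 77.5 x sqrt(1/n1 + 1/n2).

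| Arms | SE (mmHg) | Power |
|---|---|---|
| 42:42 | 16.9 | 0.84 |
| 43:42 | 16.8 | 0.84 |
| 51:34 | 17.2 | 0.83 |

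After 10% loss, 38:38 gives 0.80 and 46:31 gives 0.79. Even the outer bound costs about 0.01.

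**Predictability, for someone who knows the block size and past allocations.**
- *Blocks of five, random direction:* slot 4 is certain if the first three agree (probability 0.1), and slot 5 is certain if the first four split 3:1 (probability 0.4). The fully determined share is (0.1 + 0.4)/5 = 10%.
- *Fixed blocks of four:* slot 3 is certain with probability 1/3 and slot 4 always, so (1/3 + 1)/4 = 33%.

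**The case against.** Several points can fairly be made for the plan, and most of them limit the finding.

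- **1:1 may still hold as a probability.** If the 3:2 direction is random per block, each patient has probability one half of either arm. A reader might infer that the scheme makes 1:1 impossible. The documents do not support that: what is lost is guaranteed equal arms, not a 1:1 target. The article does not say that the direction is random.
- **The extra slot may be harmless.** Seventeen is the smallest number of five-patient blocks that covers 84, so one unused envelope is a natural reading. Alone, 85 against 84 is minor. It does not explain the odd block size.
- **A 51:34 split should not be inferred.** It needs the same arm to receive three in every block, against the ratio stated in the preceding sentence.
- **Unequal arms do not bias the comparison.** The planned independent-samples t test does not need equal groups, and the power loss is about 0.01. A reader might infer a threat to the trial's conclusion; the figures do not show one.
- **The odd size does not make allocation easier to guess.** Under the random-direction reading it determines fewer slots than fixed blocks of four (10% against 33%). Predictability comes from any single fixed block size combined with open delivery, since whoever ventilates the patient sees whether a recruitment maneuver is done. The envelopes are sealed and opaque, and the article does not say that recruiting staff know the block size.

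None of this removes the core: the block size, block count, ratio and totals do not fit together, and nothing in the article reconciles them.

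**Conclusion.** The allocation scheme is wrong as written. Blocks of five cannot be balanced between two arms at 1:1, and 17 of them do not total 84, so the described list cannot guarantee 42 per arm. Exactly 42:42 could still arise by chance or through an arrangement that the article does not disclose.

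The size depends on the missing rule. Alternation leaves a one-patient difference over the full list; a random direction per block gives an SD of 4.1 and a 33% chance of a difference of 5 or more. The consequence for power is small (0.84 against 0.83 at the outer bound, at an assumed SD of 77.5 mmHg), and there is no direct bias. Severity is moderate: a specification defect that should be corrected because it leaves the allocation impossible to audit from the published description.

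**What to change.** Reconcile the randomization section with the Abstract, Objectives and design, and Sample size calculations by using even blocks that total 84. Randomly ordered blocks of 4 and 6 are preferable, with sizes concealed from recruiting staff. For example, 9 blocks of 4 plus 8 blocks of 6 give 36 + 48 = 84 patients and 18 + 24 = 42 per arm. Twenty-one blocks of 4 or 14 blocks of 6 also give 42:42, but a single fixed size is easier to guess when delivery is open.

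First enrolment was planned for March 1, 2024, before the article appeared in July 2024, so envelopes may already be in use. In that case, check the actual list, report the block sizes and split rule used, and generate the remaining allocations in even blocks. Even blocks added after an unbalanced start do not undo the imbalance, so exact 42:42 may no longer be reached, and that should be accepted and reported.

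Cost: if the published figures are only a reporting slip, one corrected sentence. Before enrolment, a new list and envelopes as well. During enrolment, replacing the remaining allocations also needs a protocol amendment with the notifications that the article describes. The sample size does not change.

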### Data monitoring

A principal investigator and other members who take part in the design and implementation of the trial compose the research team. For the sake of quality control, a physician who does not take part in the trial will be in charge of data monitoring. Monitoring comprises evaluation of study progress and verification of precision as well as the integrity of recorded data. After completion of the study, the original data and results will be submitted to the scientific management committee, and will be disclosed to the public after publication of results.

### Auditing trial conduct

A physician independent from the investigators will be responsible for supervising the implementation of the trial and ensuring that the trial comply with the rigorous standards formulated by the state food and drug administration for good clinical practice. Trial conduct will be audited every twelve months across the trial timeline.

### Study population

Patients scheduled for elective video-assisted pulmonary lobe resection under general anesthesia will be screened and recruited during routine preoperative assessment. During recruitment, we will cooperate with surgeons to obtain detailed medical history and results of laboratory tests and radiological tests. Furthermore, we will discuss the procedures of our trial intervention with other anesthesiologists of our center, thereby receiving assistance from collegues during the trial implemention. With the help of collegues, reaching sample size wouldn’t be difficult. The inclusion criteria are as follows: 18–75 years old, American society of anesthesiologists (ASA) grade III or lower, double lumen tube used for lung isolation, length of one lung ventilation exceeding that of two lung ventilation, anticipated to undergo one lung ventilation for over an hour.

Exclusion criteria: pregnant, history of chronic obstructive pulmonary disease (COPD) (defined as GOLD grades III-IV), with pulmonary fibrosis, requiring devices other than double lumen tube for lung isolation, with bulla on the dependent lung, with severe pneumothorax or emphysema, with congestive heart failure (defined as NYHA grades III-IV), having a history of pulmonary surgery, a history of acute respiratory infection (within one month prior to surgery), dependent on renal replacement therapy, pulmonary arterial hypertension (defined as mean pulmonary arterial pressure exceeding 25 mmHg during rest or systolic pulmonary arterial pressure over 40 mmHg), known or suspected neuromuscular illnesses (thymoma, myasthenia gravis, myopathy, myodystrophy), planned for postoperative mechanical ventilation, scheduled for bilateral surgery, scheduled for surgery in prone position, sustained hemodynamic instability or refractory shock (according to the judgement by the anesthesiologist in charge), known significant lung injury (PaCO_2_ > 50 mmHg, PaO_2_ < 50 mmHg), taking angiotensin converting enzyme inhibitor (ACEI) or angiotensin receptor blocker (ARB) to treat hypertension.

Dropout criteria: unplanned thoracotomy conversion, intraoperative blood loss surpassing 500 ml.

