### Protocol deviation

Anesthesiologists can deviate from the trial protocol whenever concerns over patients’ safety emerge. During one lung ventilation, if hypoxemia(SpO_2_ < 92%) persists after excluding displacement of double lumen tube, rescue recruitment maneuvers could be performed. Subsequently, two lung ventilation can be resumed temporarily in case hypoxemia is not corrected. Patients who deviate from the protocol will be excluded from the final analysis.

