#### Strategies to improve adherence

The two main reasons for investigators to deviate from trial protocol are the occurrence of hemodynamic instability and refractory hypoxemia. So, during the pre-op visit, patients at risk for massive bleeding and hemodynamic instability should be identified. In addition, patients should be screened for risk factors of hypoxemia during one lung ventilation.Protocol amendments.

The primary investigator would notify all members of the research team, the ethics committee, and the surgeons, nurses and other anesthesiologists of our center who provide assistance to the implementation of the trial. After notification, a copy of the revised protocol would be added to the investigator site file.

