### Statistical analysis

The research team will cooperate with medical statisticians to analyze data after completing the trial. SPSS 20.0 software will be applied for data processing. Dropout or lost to follow up cases will be reported. Per-protocol analyses will be applied for all data. Under circumstances of missing values, multiple imputation shall be conducted. Kolmogorov–Smirnov analysis will be performed to discern normally distributed data. Normally distributed data will be presented as mean $$\pm$$ standard deviation (SD), while discrete data will be presented as median and interquartile range. Independent-samples T test will be adopted for univariate analysis of normally distributed data. Pearson correlation test will be used to test the linear relationship between two variables. Mann–Whitney U test will be applied for discrete data. Categorical variables will be expressed as relative risk ratio and assessed by Fisher’s exact test or chi-square tests, if applicable. 95% CI will be employed to express confidence level of all parameters. *P* value < 0.05 shall be defined as statistically significant.

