Recruitment maneuver could lead to temporal hemodynamic instability. Hence, the ideal recruitment maneuver eliminates atelectasis with the lowest effective peak inspiratory pressure and fewest numbers of breaths or shortest effective time [20]. Yet, evidence on the effective time and effective peak inspiratory pressure during recruitment maneuvers are still lacking. Although, the advantages of individualized PEEP has been proven by numerous studies, recruitment maneuvers applied in the majority of studies are unindividualized. Wu and collegues compared the effects of traditional recruitment maneuvers and ultrasound guided recruitment maneuvers on patients undergoing thoracic surgery [21].They discovered that, the incidence and severity of atelectasis are lower in patients receiving ultrasound guided recruitment maneuvers than those receiving conventional recruitment maneuvers. Therefore, unindividualized recruitment maneuvers may not be effective in recruiting all collapsed alveoli and thus has limited benefit. On the other hand, the pressure and time of unindividualized recruitment maneuvers may be excessive, aggrevating its potential harm.

Ideally, satisfactory collapse of the independent lung would be achieved to facilitate surgical procedure, while the atelectasis of the dependent lung is minimized to improve oxygenation and ventilation mechanics. Inhaling pure oxygen would facilitate the development of atelectasis, which plays a key role in the phase II collapse of the independent lung [22]. On the other hand, limiting the fraction of inspired oxygen could alleviate atelectasis [20].Thus, before placing the patient in lateral decubitus position, we lowered the fraction of inspired oxygen during ventilation of the dependent lung to avoid formation of atelectasis during adjustment of the position of the double lumen tube which necessities temporal disconnection from the ventilator. While the independent lung is ventilated with pure oxygen to facilitate the development of atelectasis.

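### Patients removed for instability-driven deviation, blood loss over 500 ml or thoracotomy conversion leave every between-group comparison, including those of hypotension, PPCs, ICU transfer and adverse events

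*Protocol article*

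**What the plan says.** Four statements in the protocol article act together.

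- Study population: "Dropout criteria: unplanned thoracotomy conversion, intraoperative blood loss surpassing 500 ml". Both are intraoperative events and so arise after a patient has entered the trial.
- Protocol deviation: "Anesthesiologists can deviate from the trial protocol whenever concerns over patients’ safety emerge", and "Patients who deviate from the protocol will be excluded from the final analysis".
- On adherence, the article adds that the chief causes of such departures "are the occurrence of hemodynamic instability and refractory hypoxemia" (Strategies to improve adherence).
- Statistical analysis: "Per-protocol analyses will be applied for all data". No other analysis set is named for any endpoint. The same section adds "Dropout or lost to follow up cases will be reported" and provides multiple imputation for missing values.

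The Study endpoints section makes incidence and duration of hypotension and of hypoxemia, ICU transfer, ICU and hospital stay, adverse events and PPCs secondary endpoints. Under Study visits and data collection, adverse events are followed from the start of the intervention to discharge.

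**The concern.** For a safety or clinical endpoint, being analysed should not depend on whether the harm occurred. Here it can. A patient whose instability is severe enough to make the anesthesiologist leave the protocol is excluded, and so drops out of the hypotension comparison because of hypotension. A patient who bleeds more than 500 ml or is converted is plausibly at higher risk of a PPC or ICU transfer, yet is not counted for either. Bleeding or conversion can also come after the T4 sample, when the intervention has been delivered and the primary measurement taken.

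The arms may not be affected alike. By protocol only the control arm receives the recruitment maneuver, and the Discussion says "Recruitment maneuver could lead to temporal hemodynamic instability". The article presents the study strategy as a way to avoid the harms of that maneuver, so the comparisons at risk are the ones that would show whether it does.

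**Working it through.** **1. Does any provision return the excluded patients to a comparison?**

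- Reporting dropouts gives counts of cases. It does not put their outcomes into a comparison.
- Multiple imputation fills missing values among analysed patients. These patients are excluded, and their values may well exist.
- Monitoring adverse events to discharge means the data are collected. Nothing exempts them from the per-protocol rule.
- The Anesthesia section sets out how hypotension is managed within the protocol. Patients managed that way have not deviated and stay in. The loss is confined to cases that led to deviation, heavy bleeding or conversion.

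**2. How many patients does the plan expect to lose?**

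Inputs from Sample size calculations: 38 per group, a 10% removal and dropout rate, 42 per group.

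- Reproducing the 42: 38 × 1.1 = 41.8, rounded up to 42. Dividing instead, 38 / 0.9 = 42.2, rounded up to 43. The stated figure follows from the first form.
- Planned loss: 42 − 38 = 4 per group, or 8 in total; equivalently 84 × 0.10 = 8.4. This covers removal for all reasons.

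**3. What could the loss of 8 patients do?**

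The event counts below are assumptions, since the article gives none. As an extreme case, all 8 removed patients had the event. Analysed rate = (events − removed) / (42 − removed), shown as control v study.

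| Assumed truth | Removed, control:study | Analysed | Rates |
|---|---|---|---|
| 8/42 v 8/42 (19.0% each) | 4:4 | 4/38 v 4/38 | 10.5% v 10.5% |
| | 6:2 | 2/36 v 6/40 | 5.6% v 15.0% |
| | 8:0 | 0/34 v 8/42 | 0% v 19.0% |
| 12/42 v 6/42 (28.6% v 14.3%) | 4:4 | 8/38 v 2/38 | 21.1% v 5.3% |
| | 6:2 | 6/36 v 4/40 | 16.7% v 10.0% |
| | 8:0 | 4/34 v 6/42 | 11.8% v 14.3% |

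The pooled rate falls in every row: from 16/84 = 19.0% to 8/76 = 10.5%, and from 18/84 = 21.4% to 10/76 = 13.2%. The contrast has no fixed direction. In the second block a true difference of 14.3 points becomes 15.8, 6.7 or −2.5.

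**4. Does the effect measure matter?**

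Suppose instead that the same fraction f of hypotensive patients is removed in each arm. Analysed rate = p(1 − f) / (1 − pf), with assumed true rates p of 30% (control) and 10% (study), a difference of 20 points and a ratio of 3.00.

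- f = 0.25: 0.225/0.925 = 24.3% v 0.075/0.975 = 7.7%. Difference 16.6 points, ratio 3.16. Removed: 7.5% and 2.5%, or 5% overall.
- f = 0.50: 0.15/0.85 = 17.6% v 0.05/0.95 = 5.3%. Difference 12.4 points, ratio 3.35. Removed: 15% and 5%, or 10% overall, which uses the plan's whole allowance.

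The risk difference falls while the relative risk, the measure the plan names for categorical variables, rises. Both arms' absolute rates fall.

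**The case against.** The strongest reply is that the rule applies to both arms, the affected endpoints are secondary, and per-protocol is a recognised analysis for the non-inferiority primary endpoint. Ordinary hypotension is not a deviation, the Discussion describes instability from the maneuver as temporary, dropouts are reported, and patients at risk of massive bleeding or instability are to be identified before surgery. Bleeding and conversion are surgical events that no section links to the ventilation arm.

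Most of this stands as a limit on the point. A reader might infer that the rule selectively hides the maneuver's harms in the control arm and so narrows the difference between arms. The documents do not support that. Study-arm deviators are removed too, no expected deviation rates by arm are given, and the working shows that the contrast can widen, narrow or reverse and that relative risk and risk difference can move in opposite directions. A reader might also infer that these patients vanish from the report or that their follow-up stops. The article says neither.

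The objection does not justify a single per-protocol set for every endpoint. The case for per-protocol in non-inferiority concerns the oxygenation index at T4; it does not extend to safety and clinical outcomes. Nor can this be left to an analysis plan that is not shown, because a safety set including these patients would contradict what the article states.

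**Conclusion.** The point holds in limited form. As written, the plan takes out of every between-group comparison the patients whose hemodynamic instability led to a deviation, who bled over 500 ml or who were converted. Absolute rates of hypotension, PPCs, ICU transfer and adverse events are therefore likely understated, on the plausible assumption that the removed patients carry more of these events than those who remain. Bias in the arm comparison is possible, because only the control arm receives the maneuver by protocol, but its size and direction cannot be derived from the documents. The expected scale is about 8 of 84 patients for all reasons; the rates in the working rest on assumed counts and show what could happen, not what will.

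**What to change.** In Protocol deviation and in Statistical analysis, state that hypotension, hypoxemia, PPCs, ICU transfer, length of stay and adverse events are analysed by allocated arm in all randomized patients in whom one lung ventilation was started, regardless of deviation, blood loss or conversion. Report conversion and blood loss over 500 ml by arm. State that the dropout criteria do not remove patients from this analysis set, and that T4 values drawn before the event are kept. The criteria themselves need not be deleted. Per-protocol can stay as an analysis of the non-inferiority primary endpoint and as a second presentation of the other endpoints.

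The cost is wording. The sample size does not change, and visits on postoperative days 1 to 3 and at discharge are already planned. The downside is that PPC and ICU rates will be somewhat higher and will include surgery-related events.
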